### Strengths and Limitations

Even though the present study will show evidence of *S. maxima* supplementation’s clinical importance, the variety of bioactive compounds contained in *S. maxima* limits the possibility of establishing clear and specific action mechanisms. Concerning to the inclusion criteria, only sedentary older adults with BMI over 25 kg/m^2^ will be selected, so the overall results may not translate to other populations of older adults. Another limitation is that the randomization will not be applied to define the inclusion or not in the exercise program intervention, it will be decided by each participant since the personal decision to belong to the exercise group will reduce severely the possibility of study desertion [40,41]. In addition, the beneficial effects associated with healthy lifestyles (physical exercise and nutraceuticals) underlie major causes such as sociodemographic characteristics of the participants, timing of the intervention, dose of supplementation, environmental factors, and genetic background [42]. Previous studies display a considerable amount of risk of bias, such as selection bias (e.g., recruitment of an over-proportionated number of women) and performance bias (e.g., unclear methods of blinding and concealment). Therefore, a proportional number of women and men will be included in this study. Regarding the sample size, the duration of the intervention and the quantity of *S. maxima* to administrate, double-blind studies have reported on the benefits of four weeks of supplementation with nine participants [43], and other studies have reported on the beneficial effects of supplementation with one g/day of *S. maxima* for 12 weeks [44]. All this establishes the importance of this study.

## 4. Conclusions

The SIE study protocol design includes multidisciplinary interventions to define potential future implementation of nutritional supplementation programs with natural products containing a high content of antioxidants and/or proteins, along with personalized exercise programs, in the elderly presenting the main risk factor (excess body fat) of chronic non-communicable diseases. However, possible practical applications could be ensured until results are obtained, where it is expected to have a beneficial impact in all the study’s analysis (body composition, physical capacities, blood lipid profile, mental health, sleep-wake patterns, and inflammatory markers). Finally, the future research lines generated by the SIE project can focus on the inclusion of a more significant number of parameters related to exercise prescription, such as epigenetics, intestinal microbiota, and general fitness. Studies can also be designed to look for long-term effects, including different age groups, or present other pathological conditions. Moreover, the amount of recollected data will allow us to build a dataset, then we will make it available to the Artificial Intelligence community in order to find predictive models.

## Figures and Tables

**Figure 1 ijerph-18-01605-f001:**
[figure not shown]
Flow diagram of the experimental design for the impact of *Spirulina maxima* intake and exercise (SIE) trial. Same color indicates the same group of participants.

**Table 1 ijerph-18-01605-t001:** Inclusion and exclusion/elimination criteria to participate in the *Spirulina maxima* intake and exercise (SIE) randomized controlled trial.

Inclusion Criteria	Exclusion/Elimination Criteria
Man or woman	Drinking alcohol
≥60 years	Taking drugs or diet supplements
Daily energy expenditure <4 metabolic equivalents	Presenting an impediment to practicing regular physical exercise
Body mass index≥ 25 kg/m^2^	Participate in any other interventional study
Signed informed consent	<80% attendance to exercise sessions
	Being unhealthy due pre-intervention test results by certified doctor’s decision
	Fracture or surgery in the last six months
	Presenting a chronic disease
	Present a risk when increasing exercise level and/or engage in fitness testing (Physical Activity Readiness-Questionnaire for Everyone (PAR-Q+) with at least one “yes” answer in any of seven pre-screening questions and at least one “yes” in one of the next 10 follow-up questions) [21]

**Table 2 ijerph-18-01605-t002:** Summary of the independent and dependent variables of the *Spirulina maxima* intake and exercise (SIE) randomized controlled trial.

Independent Variables	Dependent Variables
*Spirulina maxima* intake intervention	Body composition (body fat percentage, muscle mass percentage, and body mass index)
Exercise program intervention	Energy intake (total calories, proteins, carbohydrates, fat, and micronutrients consumption)
Wash-out period	Physical function (grip strength and functional physical condition)
Genetic markers	Blood lipid profile (TC, HDL-C, LDL-C, and TG)
	Mental health (anxiety, depression, and cognitive performance)
	Sleep-wake patterns
	Inflammatory markers (IL-6 and TNF-α)

TC: Total cholesterol; HDL-C: High-density lipoproteins associated cholesterol; LDL-C: Low-density lipoproteins associated cholesterol; TG: Triglycerides.

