### 2.1. Eligibility Criteria

Fifty-two sedentary (daily energy expenditure <4 METs, as measured by a continuous physical activity questionnaire (IPAQ)) [20] older adults (≥60 years) with a BMI over 25 kg/m^2^ volunteered to participate will be recruited by personalized interviews including a Physical Activity Readiness-Questionnaire for Everyone (PAR-Q+) [21] conducted to ensure eligibility. The participants inclusion and exclusion/elimination criteria are depicted in Table 1.

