### 2.2. Interventions

The clinical trial consists of two interventions: (1) supplementation with *S. maxima* (5 g/day) or placebo (5 g/day of a low-calorie saccharine), and (2) an exercise program, during a period of 24 weeks in a randomized, double-blind, counterbalanced, crossover, controlled trial with a 2 × 2 factorial design. Presentation of both supplements will be powder encapsulated in dark capsules of 0.5 g to present the same organoleptic attributes and mask their individual characteristics.

Inclusion in the exercise program intervention will be decided by each participant, who will be randomly assigned to one of the two possible nutritional interventions (*S. maxima* or placebo) categorized into four treatments: an exercise program plus *S. maxima* intake; exercise with placebo administration; *S. maxima* intake without exercise, or placebo supplementation without exercise program (Control). To assess compliance to the supplement intake, a crossover will be conducted for the supplementation interventions.

The first period of treatment will be carried out for 12 weeks, followed by a four-week wash-out period to avoid any possible delayed effect of *S. maxima* in the organism. Finally, a further 12 weeks of treatment for the second intervention groups (Figure 1).

Due to absence of data related to wash-out and treatment periods length, we considered 4 and 12 weeks, respectively, as stated by a systematic review of clinical trials that used spirulina as treatment [22].

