#### 2.2.1. Exercise Program

Participants in the exercise program groups will exercise five days a week. The physical activity program will be conducted in accordance with the American College of Sports Medicine recommendations [23] and will consist of Monday to Friday chair exercises performed during 24 weeks.

The approximate exercise duration will be of 40–50 min. Each exercise session has an initial or warm-up phase of 5–10 min (joint movement exercises to increase body temperature starting with movements of head, upper extremities trunk, hip, and, lower extremities); a main physical conditioning phase of 25–30 min that will consist of developing a personalized circuit of strength exercises of the main muscle groups (arms, shoulder, chest, back, and legs) at moderate intensity (between 3.0 and 6.0 metabolic equivalents of task (METs)) using rating of perceived exertion scale and the Talk Test; finally, a cool-down or relaxation phase of 5–10 min. To define the individual exercise intensities in the main physical conditioning phase, participants will have a training of 3 to 5 days before the beginning of the clinical trial to learn how to use the rating of perceived exertion scale and the Talk Test as markers of exercise training intensity.

Trained personnel will assist older adults to perform the exercise program, including articular flexibility, postural exercises, and proprioception exercises. These activities will be selected according to the individual deterioration and joint stiffness that the participants could present. Researchers are trained in cardiopulmonary resuscitation and the laboratory has the necessary tools and communication channels to carry out emergency procedures if a participant presents any side effect of exercise.

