### 2.6. Statistical Methods

Normality and homoscedasticity of variables will be screened by the Shapiro–Wilk and the Levene tests, for each group. The analysis of statistical differences among treatments and time, univariate repeated measures ANOVA with two within-participants (initial and final values), and four inter-participants (treatments) factors will be used. Moreover, basal and post-treatment values will be contrasted by paired *t*-tests. Delta values will be analyzed by one-way ANOVA and Tukey Post-hoc tests (normal distribution and equal variances) and Kruskal-Wallis H and Dunn’s Post-hoc test (non-parametric distribution and unequal variances), with Bonferroni setting for multiple comparisons. Spearman correlations will be run to evaluate the associations among variables. Eventual gen-diet and gen-exercise interactions concerning anthropometric and metabolic outcomes will be assessed by univariate regression analyses. Statistically significance will be set at a *p*-value of 0.05. All statistical analyses will be completed using IBM SPSS package version 23 (SPSS Inc, IBM Company, Chicago, IL, USA) and STATA software (StataCorp, College Station, TX, USA).

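### Table 1 eliminates exercisers with under 80% attendance, a selection made after allocation that only the exercise groups face and that is likely to flatter the exercise and combined effects

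*Protocol article*

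**What the plan says.** Section 2.1 refers the reader to Table 1 for eligibility: "The participants inclusion and exclusion/elimination criteria are depicted in Table 1". The table is titled "Inclusion and exclusion/elimination criteria to participate in the *Spirulina maxima* intake and exercise (SIE) randomized controlled trial", and one entry in its exclusion/elimination column is "<80% attendance to exercise sessions".

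Section 2.2.1 shows who has sessions to attend: "Participants in the exercise program groups will exercise five days a week", with "Monday to Friday chair exercises performed during 24 weeks". Section 2.2 leaves exercise to the participant: "Inclusion in the exercise program intervention will be decided by each participant". Only the supplement is randomised, and it is crossed over.

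Section 2.2.2 assesses supplement adherence by counting returned capsules and gives no level below which a participant is eliminated. Section 2.5 repeats the assessments on days 84, 112 and 196.

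Section 2.6 compares the treatments by repeated measures ANOVA with "two within-participants (initial and final values") and four treatment groups, and by one-way ANOVA on the changes. The limitations section acknowledges that "randomization will not be applied to define the inclusion or not in the exercise program intervention". It does not mention elimination for low attendance.

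**The concern.** Most entries in that column can be judged at screening. Attendance at a 24-week programme cannot. Placed in an elimination list, it removes people on something that happens after allocation, and from only two of the four treatments.

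The main objective is the independent and synergistic effect of S. maxima with and without exercise on body composition. If the less compliant leave the exercise groups while the less compliant non-exercisers stay, part of any difference between them reflects who remained and not what exercise did. The expected direction favours the trial's hypothesis. The limitations section does not cover this: choosing to exercise is one selection, and being removed for attending too little is another.

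**Working it through.** **When and to whom the rule applies.** Inputs from section 2.2.1: 5 sessions a week for 24 weeks.

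- Total sessions: 5 × 24 = 120. The 80% level is 0.8 × 120 = 96, so missing more than 24 triggers the rule.
- Counted per 12-week period: 5 × 12 = 60, and 0.8 × 60 = 48.

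The article does not say which count is meant. Either way, the result is known only well after allocation.

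**Symmetry across the four treatments.**

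| Treatment | Sessions to attend | Elimination for low attendance | Capsule-count threshold |
|---|---|---|---|
| Exercise + S. maxima | yes | yes | none |
| Exercise + placebo | yes | yes | none |
| S. maxima, no exercise | no | cannot apply | none |
| Placebo, no exercise | no | cannot apply | none |

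**Illustrative size.** The article gives no elimination rate and no relation between attendance and outcome, so both are assumed. Let attendance and outcome (higher is better) be jointly normal with correlation r, and remove the lowest fraction q of attenders. The mean of those kept exceeds the mean of all exercisers, in outcome SD units, by

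bias = r × φ(z_q) / (1 − q),

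where z_q is the normal quantile at q and φ the normal density. For r = 0.3:

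- q = 10%: 0.3 × 0.1755 / 0.9 = 0.06
- q = 20%: 0.3 × 0.2800 / 0.8 = 0.11 (0.105 unrounded)
- q = 30%: 0.3 × 0.3477 / 0.7 = 0.15

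A simulation with 2,000,000 draws per cell agrees:

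| Correlation r | 10% | 20% | 30% | 40% |
|---|---|---|---|---|
| 0 | 0.00 | 0.00 | 0.00 | 0.00 |
| 0.2 | 0.04 | 0.07 | 0.10 | 0.13 |
| 0.3 | 0.06 | 0.11 | 0.15 | 0.19 |
| 0.5 | 0.10 | 0.18 | 0.25 | 0.32 |

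Non-exercisers lose nobody under this rule, so the whole shift enters the exercise versus non-exercise contrast.

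**S. maxima versus placebo among exercisers.** Treat the groups as parallel, as section 2.6 does, with r = 0.3. Eliminating 20% from each arm gives a bias of 0. Eliminating 10% from one and 30% from the other gives 0.15 − 0.06 = 0.09 SD in favour of the arm that lost more. The direction is therefore not fixed: it depends on which supplement group attends less.

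**The case against.** **The article names no analysis set.** Table 1 lists criteria for taking part, section 2.6 does not say that eliminated participants' data are discarded, and an unseen analysis plan might keep them. This stands as a caution: exclusion from the analysis is what the rule implies when followed, not something the article spells out. It does not remove the point, because elimination is a stated rule. If elimination also ends the assessments, no later analysis plan can recover those visits.

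**The exercise contrast was never randomised, and the article says so.** True. The rule adds selection to a comparison already open to confounding and does not break a randomised one. The added selection is undisclosed and, unlike the free choice of exercise, can be removed without redesign.

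**The sessions could be the familiarisation days.** Sections 2.2.1 and 2.5 describe 3 to 5 days before the start. This is possible but unlikely: section 2.2.1 treats those days as training to learn the intensity scales, and the column covers elimination as well as exclusion.

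**Stronger conclusions that a reader might infer.** The documents do not support these:

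- *The S. maxima versus placebo comparison loses its randomised basis.* It loses protection, but is biased only if elimination differs by supplement, and nothing in the article indicates that it would. If a whole person is removed from a crossover, both conditions lose the same person.
- *Elimination in the second period deletes first-period data.* The text does not say this. A first-period completer has a day 0 and day 84 pair.
- *The exercise gain is inflated by 11%, 25% or 43% at 10%, 20% or 30% elimination.* This is 1/(1 − p) − 1 and needs low attenders to gain exactly nothing, so that someone attending 75% counts as unexposed.
- *Power falls by a stated amount.* The article gives neither the number of exercisers nor the effect size behind its 52 participants, so the loss cannot be calculated from it.

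**Conclusion.** The point holds. Table 1 fixes an elimination rule that operates after allocation and can reach only two of the four treatments compared in section 2.6. It is separate from the self-selection that the article concedes.

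The exercise and combined effects are likely, not certain, to be overstated: the bias requires better attenders to have better outcomes and is zero if attendance and outcome are unrelated. Its size is illustrative only, 0.06 to 0.15 SD for 10% to 30% eliminated at an assumed correlation of 0.3. Over the full assumed range, correlation 0 to 0.5 and elimination 10% to 40%, it runs from 0 to 0.32 SD. For S. maxima versus placebo among exercisers, the most that can be said is that protection is lost if elimination differs by supplement, with the direction unknown.

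**What to change.** 1. Remove the attendance line from the exclusion/elimination criteria in Table 1.
2. State that participants below 80% attendance keep the scheduled assessments on days 84, 112 and 196.
3. State that the primary analysis includes them by allocated supplement sequence and initial exercise choice, using every treatment period for which data are available.
4. Use 80% attendance only to define a per-protocol sensitivity set, and say whether it is counted over 24 weeks or within each 12-week period.

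The cost is one table line and a short statement of the analysis set, including how a participant with only one complete period enters the analysis. No visits are added to the schedule. The downside is that the estimated exercise effect may be smaller.
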